## 8.2 Known potential benefits

All participating women will be provided with basic antenatal services according to the local standard of care. Participants may also benefit from the knowledge that they are assisting in the evaluation of potentially valuable methods for prevention and control of malaria for pregnant women in endemic areas.

## 8.3 Data safety and monitoring board (DSMB)

To ensure the quality and integrity of data, and the safety of participants, an independent study monitor will be contracted for the duration of the study. The monitoring group will be identified and engaged following standard WHO/TDR procedure.

**9 FOLLOW-UP**

No formal study follow-up is planned for participants after delivery, as described in 7.5.

**10 DATA MANAGEMENT**

**10.1 Data quality assurance and monitoring**

Study staff and relevant health center staff will be educated in the study protocol prior to the start of study activities at each site. Data collection forms will be reviewed by the Study Coordinators and Principal Investigators (PIs) for completeness and accuracy. PIs from the different countries will maintain regular contact to ensure consistency in protocol implementation at each site, and PIs will meet regularly with study staff at their site/s to ensure consistency in the collection of data. PIs will participate in regular study group meetings to assess progress of the study, address any difficulties with the RDTs or protocol, and provide feedback to members of the study group. A two-week pilot period will be conducted before beginning the study at each site, which will allow the PIs and study personnel to identify and resolve potential logistical and technological problems prior to beginning data collection. Standardized protocols and SOPs will be followed for quality control/quality assurance of specimen procurement and preparation, smear microscopy, placental histology, and PCR.

**10.2 Records**

All participants will be identified by a unique identifying number throughout the study; participant names will not be recorded or entered into the computerized databases. Data collection forms will be kept in secure files at each study site. All corrections to handwritten information on data collection forms and other study documents will be made by striking through the incorrect entry with a single line and entering the correct information adjacent to it; the correction will be initialed and dated by the study staff member. For any requested information that is not obtained, an explanation will be noted on the data collection form. Electronic databases will be stored in password-protected computer files. Access to the records will be limited to study staff. The investigators and study staff will allow all requested monitoring visits, audits or reviews by relevant ethical review boards.

**10.3 Data management**

Data will be transferred from the handwritten data collection forms into a computerized database by study personnel and will be double-entered to verify accuracy. Back-up files of the database will be created after each data entry session. For quality control, check programs will be written into the databases to limit the entry of incorrect data and ensure entry of data into required fields. Electronic data records will be maintained at each site and will be transmitted to a centralized database for regular cleaning and management.

**10.4 Immediate and long-term use of the data**

Data collected in this study will be compiled, analyzed and made available to collaborating partners, ministries of health in participating countries, the WHO, and will be prepared for publication in a peer-reviewed journal. Study staff and health center staff will be informed of overall study results after data analysis has been completed. Upon completion of the study, all study documents and record forms will be filed and stored at the FIND office in Kampala or Geneva for at least 12 years. Electronic data records will be stored indefinitely by investigator/s in personal computers and external hard drives. Results of the study may be publicized in the future by collaborating partners and stakeholders as part of public health education efforts and malaria control programs.

**11 STATISTICAL CONSIDERATIONS**

Data analysis will be performed by the PIs using Stata statistical software package, with assistance from [name], of the Queensland Institute of Medical Research and other co-investigators as appropriate.

**11.1 Study outcome measures**

Results of peripheral blood tests performed during gestation will be analyzed for associations with evidence of placental malaria and pregnancy outcomes. The statistical analysis will focus on three primary outcomes: 1) negative predictive power of malaria RDTs, peripheral blood films and PCR performed on peripheral blood to diagnose placental malaria during gestation, 2) association of placental malaria during gestation on mean infant birth weight and 3) association of placental malaria during gestation on mean maternal Hb. These outcomes will be used to assess the potential utility of RDTs as screening tests to identify clinically significant malaria infections at a time when effective preventive measures may be taken. Other factors known to influence the study outcomes, including iron and folate supplementation, bed net use and administration of antihelminthic drugs will be treated as confounders in the analysis. In addition, stratified analysis will be conducted to assess these associations within subgroups based on geographic location, estimates of malaria endemicity, participant age, and parity (gravida class).

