**Follow up at delivery**

- Maternal peripheral blood for Hb, RDTs, smear, and PCR
- Placental blood for RDTs, smear, and PCR
- Placental tissue sample to process for histopathological examination
- Measurement of infant birth weight
- (Other data on any maternal or fetal morbidity/mortality)

1. **STUDY POPULATION**

Participants in this evaluation will include pregnant women presenting for routine antenatal services in areas of Africa where IPTp is considered standard of care according to WHO and national malaria control program guidelines. Pregnant women of any parity will be eligible for enrollment. Anticipated sites include antenatal clinics in Burkina Faso, Nigeria, and Uganda. Specific participant selection criteria will include (please see also section 7.2 on participant enrollment):

1. Presenting for care after quickening and before onset of labor (i.e. in the second or third trimester of pregnancy)
2. Age between 16 years and 44 years, inclusive
3. Willingness and ability to follow up with study visits and activities through the duration of pregnancy and at delivery
4. Absence of history of serious adverse reaction to sulfa drugs
5. Absence of history of serious adverse reaction to artemisinin-based drugs or quinine (depending on national policy on treatment of malaria in pregnancy)
6. Absence of HIV infection (both because guidelines for malaria prevention in pregnancy for HIV-infected women differ from those for HIV-negative women, and in order to avoid confounding of pregnancy outcomes by HIV-related complications or treatments in this early evaluation)
7. Absence of history of or current obstetrical complications (e.g. pre-eclampsia, eclampsia, hypertension during pregnancy, post-partum hemorrhage, evidence of multiple gestation)
8. Absence of chronic disease (e.g. diabetes mellitus, sickle cell disease)
9. Absence of evidence of severe acute disease requiring inpatient management or referral
10. Provision of written informed consent
11. Enrollment Hb ≥7 g/dL

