
At the time of delivery, placental blood and tissue sample/s will be collected and processed according to standard methods for smears, storage for molecular analysis, and for histopathological examination. Specific details of placental collection will be described in more detail in site-specific protocols; in general, for births taking place at the health center, health center staff will assist with delivery, including delivery of the placenta, and will then work with study staff to ensure the placenta is transferred to the laboratory area for processing as efficiently as possible to avoid degradation of the samples. As in section 7.5, if a participant does not deliver at the study site, study staff will attempt to visit her to obtain data and samples within 24 hours of the birth. The placenta will be wiped and washed with approximately one liter of phosphate buffered solution (PBS) to remove blood clots, placed umbilical cord side down on a clean, dry cloth, and gently blotted with a paper towel. Placental blood samples and biopsies will be collected and stored for further staining and processing. Placental histology samples will be read by two expert microscopists with discrepant results resolved by a third reader, with a proportion of samples sent to an independent research group for external quality control.

*7.6.8 Collection of data on other maternal and fetal outcomes*

In addition to the specific assessments described above, data on other significant maternal and fetal outcomes will be collected. In particular, the study staff will endeavor to collect data on management of any febrile or afebrile illnesses during pregnancy, and on birth outcomes including requirement and rationale for Cesarean section, any obstetrical complications, and fetal or maternal death. If a participant does not return to the health center at the anticipated time of delivery, study staff will contact the participant by phone and/or conduct a home visit to attempt follow-up. A participant will be considered lost to follow-up if no data can be collected within 7 days of delivery; within the 7-day limit, complete or partial data (e.g. maternal blood and infant weight, but no placenta) may be collected.

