**11.2 Analysis plan**

The unit of analysis will be each pregnancy. For each pregnant woman a complete data set consists of the following:

| Variable | Type of data | Variable classification | | | | |
| --- | --- | --- | --- | --- | --- | --- |
| Confounder | Evidence of placental malaria | Outcome measure | | |
| Predictive value of diagnostic | Infant birth weight | Maternal Hb |
| RDT on peripheral blood taken during 2nd trimester | Binary (positive / negative) |  |  | X |  |  |
| Microscopy of peripheral blood taken during 2nd trimester | 1. Binary (positive / negative)  2. Count for positives |  |  | X |  |  |
| PCR on peripheral blood taken during 2nd trimester | Binary (positive / negative) |  | X |  |  |  |
| RDT on peripheral blood taken during 3rd trimester | Binary (positive / negative) |  |  | X |  |  |
| Microscopy of peripheral blood taken during 3rd trimester | 1. Binary (positive / negative)  2. Count for positives |  |  | X |  |  |
| PCR peripheral blood taken during 3rd trimester | Binary (positive / negative) |  | X |  |  |  |
| RDT on peripheral blood taken during or shortly after delivery | Binary (positive / negative) |  |  | X |  |  |
| Microscopy of peripheral blood taken during or shortly after delivery | 1. Binary (positive / negative)  2. Count for positives |  |  | X |  |  |
| PCR result on peripheral blood taken during or shortly after delivery | Binary (positive / negative) |  | X |  |  |  |
| Placental histology for evidence of infection | Binary (positive / negative) |  | X |  |  |  |
| Diagnostic results of any additional visits to clinic (eg symptomatic infection) | Binary (positive / negative) |  | X |  |  |  |
| Maternal Hb at delivery | Continuous |  |  |  |  | X |
| Infant birth weight at delivery | Continuous |  |  |  | X |  |
| Study site | Nominal | X |  |  |  |  |
| Age | Continuous | X |  |  |  |  |
| Gravidity | Ordinal | X |  |  |  |  |
| SP treatment | Binary (yes/no) | X |  |  |  |  |
| Iron & folate supplementation | Binary (yes/no) | X |  |  |  |  |
| Bed net use | Binary (yes/no) | X |  |  |  |  |

The following definitions will be used:

- Evidence of placental malaria: a positive PCR result is obtained for any peripheral blood sample and / or there is evidence of placental infection by histology
- RDT positive: a positive RDT result is obtained from one or more blood samples
- Microscopy positive: parasites are detected by microscopy (thick film) in one or more of the blood samples

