The accuracy of RDTs and peripheral microscopy at detecting placental malaria will be assessed by considering the sensitivity, specificity, positive predictive value and negative predictive value of each diagnostic compared to evidence of placental malaria. This analysis will be conducted for all samples combined and also separately for each study location. Marginal generalized linear models will be developed to assess the impact of confounders on predictive values.

The impact of RDT screening and treatment compared to standard IPT on infant birth weight and maternal Hb will be assessed for non-inferiority by testing the hypotheses:

1. Mean birth weight of infants whose mothers were RDT positive & treated with ACT/quinine ≥ mean birth weight of infants whose mothers were RDT negative (and received SP)
2. Mean Hb of mothers who were RDT positive & treated with ACT/quinine ≥ mean Hb of mothers who were RDT negative (and received SP)

Standard statistical techniques such as t-tests, ANOVA and regression modeling will be used to test these hypotheses and investigate the potential impact of confounders on birth weight and maternal Hb.

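### Sections 11.1 and 11.2 name different exposures for birth weight and maternal Hb, so 11.2 specifies no analysis of primary outcomes 2 and 3 as 11.1 defines them

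*Protocol*

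**What the plan says.** Protocol section 11.1 lists three primary outcomes. The second is the "association of placental malaria during gestation on mean infant birth weight" and the third the "association of placental malaria during gestation on mean maternal Hb". The section opens more generally: "Results of peripheral blood tests performed during gestation will be analyzed for associations with evidence of placental malaria and pregnancy outcomes". It names iron and folate, bed net use and antihelminthic drugs as confounders, and adds that "stratified analysis will be conducted to assess these associations within subgroups".

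Section 11.2 does not define placental malaria during gestation as such. It defines evidence of placental malaria: "a positive PCR result is obtained for any peripheral blood sample and / or there is evidence of placental infection by histology". The peripheral samples include those from the second and third trimesters and from delivery. The placenta itself is sampled once. Section 7.6.7 says "At the time of delivery, placental blood and tissue sample/s will be collected and processed according to standard methods", and the delivery box of Figure 1 lists "Placental tissue sample to process for histopathological examination".

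For birth weight and Hb, section 11.2 states two non-inferiority hypotheses on screening and treatment compared with standard IPT. The first begins "Mean birth weight of infants whose mothers were RDT positive & treated with ACT/quinine" and sets this mean against that of infants of RDT-negative women who received SP. The second has the same form for maternal Hb. The t-tests, ANOVA and regression named next are for testing these hypotheses and examining confounders.

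Section 4.1 places birth weight and maternal Hb under the secondary objectives.

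**The concern.** The exposure in the outcome definition is placental infection. The exposure in the stated tests is RDT result together with the treatment that follows from it. These are different questions. The first asks whether placental infection goes with lower birth weight or Hb in this cohort. The second asks whether women who were screened positive and treated do as well as women who screened negative.

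Section 11.1 says the primary outcomes will be used to judge whether RDTs find clinically significant infections. That argument needs the link from placental infection to outcome. If only the RDT-group comparison is run, a small or null difference among treated women could be reported as the primary result and read as little effect of placental malaria. Whoever writes the detailed analysis cannot tell from the protocol which exposure is meant.

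**Working it through.** **Step 1: the two sections side by side.**

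| | Section 11.1, outcomes 2 and 3 | Section 11.2, stated hypotheses |
|---|---|---|
| Outcomes | Mean birth weight, mean maternal Hb | Mean birth weight, mean maternal Hb |
| Exposed | Placental malaria during gestation | RDT positive and treated with ACT/quinine |
| Comparison | Not stated; by implication, no placental malaria | RDT negative, given SP |
| Question | Association | Non-inferiority |

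In 11.2, evidence of placental malaria appears only as the reference standard for sensitivity, specificity and predictive values. No sentence there sets birth weight or Hb against it.

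**Step 2: the plan's own figures.** Section 11.3 gives detectable differences of 85 g and 0.34 g/dl for the whole study. It gives neither standard deviations nor the share of women exposed, so these cannot be reproduced. With 1,665 × 0.85 = 1,415 evaluable women, 80% power and two-sided 5% (the sidedness is assumed), the implied SD is difference × √(N·p·(1−p)) / (1.960 + 0.842), where p is the exposed share:

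- p = 10%: 342 g and 1.37 g/dl
- p = 25%: 494 g and 1.98 g/dl
- p = 50%: 571 g and 2.28 g/dl

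The figures are attainable under some inputs, but 11.3 does not say whether they refer to the placental-malaria contrast or the RDT-group contrast. It therefore does not settle which exposure is meant.

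**Step 3: are the contrasts interchangeable?** Let d be the mean difference between women with and without placental malaria. If RDT error is unrelated to outcome and treatment has no effect, the RDT-positive mean is shifted by PPV·d and the RDT-negative mean by (1−NPV)·d. The RDT-group difference is therefore (PPV + NPV − 1)·d.

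Inputs: sensitivity 0.65 and specificity 0.98 (section 11.3). Prevalence π is assumed from 10% to 40%; section 3.1.1 puts infection at delivery at about one in four in stable-transmission areas without prevention.

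- P(RDT+) = 0.65π + 0.02(1−π)
- PPV = 0.65π / P(RDT+)
- NPV = 0.98(1−π) / (1 − P(RDT+))

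| π | P(RDT+) | PPV | NPV | PPV + NPV − 1 |
|---|---|---|---|---|
| 10% | 0.083 | 0.783 | 0.962 | 0.74 |
| 20% | 0.146 | 0.890 | 0.918 | 0.81 |
| 25% | 0.178 | 0.915 | 0.894 | 0.81 |
| 30% | 0.209 | 0.933 | 0.867 | 0.80 |
| 40% | 0.272 | 0.956 | 0.808 | 0.76 |

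For π = 25%: 0.1625 / 0.1775 = 0.915; 0.735 / 0.8225 = 0.894; the sum less 1 is 0.81.

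**Step 4: treatment.** Sections 7.3.3 and 7.4.3 give curative treatment after a positive RDT at an antenatal visit. The RDT-group contrast therefore mixes infection with its treatment, which the factor above leaves out.

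**The case against.** The best defence is that the ingredients are all present. Section 11.1 says the associations will be analysed and stratified. Section 11.2 defines evidence of placental malaria, and its table lists the components, both outcomes and most of the confounders. Only a sentence linking them is missing, and model detail is often left to a separate analysis plan. This is right as far as it goes. It does not remove the conflict, because 11.2 is not silent on birth weight and Hb: it states hypotheses on another exposure and ties its methods to them.

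A reader might go further and infer that no visit measures the exposure. The documents do not support that. No antenatal visit samples the placenta, but the 11.2 definition counts peripheral PCR from the second- and third-trimester visits, and section 3.1.2 says histology can confirm previous as well as current infection. The exposure is measured by a proxy that mixes evidence from gestation and from delivery.

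A reader might also infer that two of the three primary outcomes will never be estimated. Section 11.1 promises the associations, so this too goes beyond the text.

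The arithmetic has limits that the objection rightly presses. The 65% and 98% are not shown to hold for a woman classed positive on any sample during pregnancy. If RDTs mainly miss low-density infections with less effect on birth weight, the shrinkage would be smaller. The ratio is also not turned into grams here: the 123 g in section 11.3 is called a likely change without naming a contrast.

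**Conclusion.** The inconsistency stands. For birth weight and maternal Hb, 11.1 names placental malaria as the exposure and 11.2 tests RDT and treatment group, so the primary contrast is not fixed. The words during gestation add an undefined term, and the primary label in 11.1 sits against the secondary objective in 4.1.

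On size, the RDT-group difference would be roughly a fifth to a quarter smaller than the placental-malaria difference (factor 0.74 to 0.81). That rests on the assumed prevalence range, on accuracy figures carried over from 11.3, on RDT error unrelated to outcome, and on no treatment effect. It shows that one contrast cannot stand in for the other; it is not a forecast of the trial's result. The point should be corrected before analysis.

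**What to change.** - **Section 11.1:** replace placental malaria during gestation with one defined exposure. This can be the PCR-or-histology composite already in 11.2, or placental histology, which is the reference in primary objective 2. Use the same definition for the predictive values, so that the term has one meaning throughout.
- **Section 11.2:** add regressions of birth weight and of delivery Hb on that exposure as the analysis of outcomes 2 and 3. Adjust for site, age, gravidity and the other confounders listed in 11.1 and in the 11.2 table.
- **RDT-group hypotheses:** keep them if wanted, but report them separately and not as the effect of placental malaria.
- **Status:** state whether birth weight and Hb are primary or secondary, and bring 4.1 and 11.1 into line.

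The cost is some rewording and two extra models on data already to be collected. If histology alone is chosen, women without a placental sample drop out of these models. Section 7.6.8 allows follow-up without a placenta, and the protocol does not say how many such women to expect.

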**7.3 Study activities and data collection at initial visit**

*7.3.1 Clinical data collection*

At the time of enrollment, information will be collected from each participant on her medical and pregnancy history, and a brief clinical assessment will be performed by a health center staff clinician (see sample data collection form, Appendix D).

*7.3.2 Laboratory sample collection*

Study staff will collect blood from participants for use in study laboratory procedures, and will prepare the samples and conduct the diagnostic tests described; all other care will be provided by health center staff (i.e. clinicians, typically midwives and nurses, employed by the health center). Each participant will provide a 2 mL (two milliliter) venous blood sample for HemoCue hemoglobin (Hb) measurement, preparation of two RDTs, preparation of thick and thin smears for expert light microscopy, and storage in a microtainer and on filter paper for PCR (see further details in section 7.6 below). Hb and RDT results will be used in clinical management as in section 7.3.3 and 7.6.1 below; expert microscopy and PCR results will not be immediately available and will not be used in management.

*7.3.3 Administration of antimalarial medicines*

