**7.6 Specific clinical and laboratory assessments**

*7.6.1 Measurement of hemoglobin (Hb) and assessment of anemia*

At the time of each routine antenatal visit, and again at delivery, maternal blood will be used to measure hemoglobin with a HemoCue machine (Quest Diagnostics, Ängelholm, Sweden). Based on WHO definitions, a participant with Hb < 11 g/dL will be considered to be anemic, and Hb < 7 g/dL will be considered to be severe anemia. Anemia will be managed by health center clinical staff according to national guidelines for anemia in pregnancy, which may include additional iron and/or folate supplementation, and/or administration of an anti-helminthic. Data on provision of such care will be recorded (as in section 7.4 above).

*7.6.2 Rapid diagnostic tests (RDTs)*

This study will evaluate the three most commonly used antigen-detection systems in RDTs: *Plasmodium falciparum-*specific plasmodium lactate dehydrogenase (Pf-pLDH), pan-specific plasmodium lactate dehydrogenase (pan-pLDH), and histidine-rich protein 2 (HRP2). According to current test format availability, in order to obtain reliable results for HRP2, pan-pLDH and Pf-pLDH or this study, two different combination RDTs (i.e. each with two test lines detecting different antigens) will be used. RDTs will be obtained directly from their manufacturers, and will be centrally procured. For each of the two types of RDT to be evaluated, all test kits used in the study will be from a single lot. Batch numbers, expiry dates, date received, and date opened will be recorded for each package of RDTs. All study personnel will receive hands-on training in preparation and interpretation of the RDTs before the study begins.

*7.6.2.1 Quality control and storage of RDTs*

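### The variable table leaves out enrolment Hb, which every participant has, and classes SP as a confounder although in the RDT-group comparison its timing, and partly its receipt, follow from the RDT result

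*Protocol*

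**What the plan says.** Section 11.2 of the protocol sets out what a complete data set contains for each woman and assigns each variable a role. The only Hb entry is "Maternal Hb at delivery", as an outcome. Six variables are marked as confounders: study site, age, gravidity, SP, iron and folate, and bed net use. The SP row reads "SP treatment | Binary (yes/no) | X". The narrative list in Section 11.1 ("including iron and folate supplementation, bed net use and administration of antihelminthic drugs will be treated as confounders in the analysis") names antihelminthics, which the table does not have, and mentions neither SP nor Hb.

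Enrolment Hb exists for everyone. It is a selection criterion in Section 6 ("Enrollment Hb ≥7 g/dL"), Section 7.3.2 takes it from the first "venous blood sample for HemoCue hemoglobin (Hb) measurement", and Section 7.6.1 repeats the measurement: "At the time of each routine antenatal visit, and again at delivery, maternal blood will be used to measure hemoglobin with a HemoCue machine".

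Section 11.2 then tests whether mean delivery Hb in RDT-positive women treated with ACT or quinine is at least that of RDT-negative women given SP. It presents this as the effect of screening and treatment against standard IPT. Among the methods, "regression modeling will be used to test these hypotheses and investigate the potential impact of confounders on birth weight and maternal Hb".

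Sections 7.3.3 and 7.4.3 schedule SP for both groups: the same day if both RDTs are negative, and two weeks after the end of curative treatment if either is positive.

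**The concern.** Infection status, not randomisation, defines the two groups. Section 3.1.1 itself describes anaemia as a risk of malaria in pregnancy, so it is plausible that RDT-positive women enter with lower Hb. Delivery Hb then reflects where a woman started as well as what happened after treatment. Without enrolment Hb, the comparison cannot separate the two and discards precision that is already paid for.

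SP raises a different problem. In the RDT-group comparison, when a woman gets SP, and whether she needs a return visit to get it, depends on her test result. It belongs to the strategies being compared. Adjusting for it removes part of the contrast that the hypothesis is about.

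**Working it through.** **Stated figure.** Section 11.3 gives a detectable Hb difference of 0.34 g/dL at the full target of 345 + 460 + 860 = 1,665 women with 15% loss. It gives neither a standard deviation (SD) nor an RDT-positive share, so the figure cannot be reproduced. It can be solved for the SD it implies, taking n = 1,665 × 0.85 = 1,415, two-sided 5% and 80% power:

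SD = 0.34 × √(n·p·(1 − p)) / (1.96 + 0.84)

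For p = 10%, 15% and 20% RDT-positive, this gives 1.37, 1.63 and 1.83 g/dL. None is implausible, so 0.34 is taken as given.

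**Effect of adding enrolment Hb.** Two inputs are assumed, because the protocol reports neither:
- the correlation r between enrolment and delivery Hb, 0.3 to 0.5, with equal SDs so that the regression slope equals r;
- an enrolment gap of 0.4 g/dL between the groups. This borrows the size of the likely Hb change in Section 11.3; it is not a reported baseline difference.

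The adjusted detectable difference is 0.34 × √(1 − r²). The carry-over is r × 0.4.

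| r | 1 − r² | Detectable difference, g/dL | Carry-over, g/dL | Carry-over / 0.34 |
|---|---|---|---|---|
| 0.3 | 0.91 | 0.324 | 0.12 | 35% |
| 0.4 | 0.84 | 0.312 | 0.16 | 47% |
| 0.5 | 0.75 | 0.294 | 0.20 | 59% |

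**What each adjustment removes.** A simulation used a true direct effect of zero, 20% RDT-positive, an enrolment gap of 0.4 to 0.8 g/dL, a slope of 0.4 to 0.6, an SP effect of +0.3 g/dL, and SP received by 99% of negatives and 85% of positives. All inputs are assumed. The group difference was:
- unadjusted: −0.20 to −0.52 g/dL;
- adjusted for SP only: −0.16 to −0.48 g/dL;
- adjusted for enrolment Hb only: about −0.04 g/dL.

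These agree with hand arithmetic. The carry-over is 0.4 × 0.4 = 0.16 up to 0.6 × 0.8 = 0.48. The route through SP is 0.3 × (0.99 − 0.85) = 0.04. So adjusting for SP leaves the whole carry-over in place and removes only the 0.04 that comes from the strategies differing in SP receipt. Adjusting for enrolment Hb does the reverse.

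**What the SP variable would measure.** The protocol does not define its coding.
- SP at the screening visit: it is the group label (correlation −1) and the model cannot be estimated.
- Any SP, with full attendance: it is a constant.
- Any SP, all negatives treated and 80% to 95% of positives attending for it, with 10% to 50% RDT-positive: the correlation with group runs from −0.43 to −0.16, and the variance inflation factor from 1.23 to 1.03.

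**The case against.** The strongest reply is that the covariate set is not closed. Section 11.1 introduces its list as examples, Section 11.2 specifies no model, and exact covariates are often left to an SAP, which is not at hand. That stands against demanding further covariates. Gestational age, calendar month or enrolment-only co-interventions may be sensible, but their absence from the lists is not an error. It carries less weight for enrolment Hb, because the Section 11.2 table sets out the complete data set with a role for each variable and gives Hb a single entry.

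Second, enrolment Hb is not a clean baseline. It is drawn with the first RDT and may already reflect infection, and adjustment does not make infected and uninfected women exchangeable. This stands as a limit. For the association of placental malaria with Hb, the third primary outcome in Section 11.1, enrolment Hb may lie on the causal path.

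Third, on SP, a reader might infer that the RDT result decides yes or no, or that SP is nearly collinear with group. The protocol does not support either. Both groups are scheduled for SP, and collinearity arises only under same-visit coding. RDT-positive is also defined over one or more samples, so a woman who first tests positive at a later visit may have had SP before that test. Nor does it follow that SP should leave every model: in the predictive-value and placental-malaria models it can be a legitimate covariate.

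**Conclusion.** The point holds for the RDT-group comparison. The table omits a baseline value that every participant has. If RDT-positive women start lower, the planned Hb comparison counts that deficit against them. A reader might infer that the omission flatters the screening strategy; the direction is the opposite, towards a false failure of non-inferiority.

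The size, 0.12 to 0.20 g/dL of carry-over and a detectable difference of about 0.32 to 0.29 instead of 0.34 g/dL, rests wholly on the assumed correlation and the assumed 0.4 g/dL gap. The protocol does not report that RDT-positive women have lower enrolment Hb, and nothing here shows 0.34 to be wrong.

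On SP, the narrower statement stands: in these two hypotheses its timing, and partly its receipt, follow from the RDT result, so it is not a confounder there.

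**What to change.** - Add enrolment Hb to the Section 11.2 table, and enter it as a continuous covariate in the regression for the second hypothesis (maternal Hb). Note that it is drawn with the first RDT and may already reflect infection.
- Do not carry it automatically into the model of placental malaria and maternal Hb.
- Do not adjust for SP in the two RDT-group hypotheses (birth weight and Hb). Report SP doses and timing by group instead. Keep SP available for the predictive-value and placental-malaria models, with its coding defined.
- While editing, reconcile Sections 11.1 and 11.2 on antihelminthics.

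The cost is one extra covariate and some wording. Enrolment Hb is already measured, so no new data are needed.
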